## Abstract

**Background::**

Anxiety is a kind of emotional disorder caused by acute conditions or trigger. It is manifested in the components of the autonomic nervous system, for instance, stress, anxiety, nervosity, and discomfort. Most patients with anxiety are more active, nervous, and alert to various stimuli. Inappropriate management of early postoperative anxiety will not only prolong recovery but also increase the risk of other complications. We conduct a randomized clinical trial to investigate the influences of nursing visits against the preoperative anxiety and postoperative complications in patients undergoing laparoscopic cholecystectomy (LC).

**Methods::**

This is a single center, placebo-controlled randomized trial, which will be performed from August 2020 to December 2020. The trial is performed in accordance with the SPIRIT Checklist for randomized studies. It is authorized by the Ethics Committee of Taizhou Hospital of Zhejiang Province (D20211-34). Two hundred patients undergoing LC will be included in this study. Patients are randomly divided into 2 groups: experiential group (n = 100) or control group (n = 100). The experimental group is given preoperative nursing visit to each patient 1 day before the operation, whereas the control group did not receive the preoperative nursing intervention. The patients in experience group also received education on the surgery team and the environment of operating room, the process of anesthesia, advantages of laparoscopic surgery, and the postoperative care from recovery room to discharge. The primary outcomes include State-Trait anxiety level and postoperative visual analogue scale. Secondary outcomes include total consumption of analgesics and postoperative complications.

**Results::**

Figure (a) will show the comparison of outcomes between 2 groups.

**Conclusion::**

The preoperative nursing visit may decrease the anxiety and the complications after operation in patients receiving LC.

**Trial registration::**

This study protocol is registered in Research Registry (researchregistry5924).

## Introduction

1

Laparoscopic cholecystectomy (LC) was conducted for the first time in 1987,^[1]^ and it is now a successful surgical method to treat the biliary colic, cholecystitis, and cholelithiasis.^[2–4]^ The popularization rate of LC is getting higher and higher, which is mainly because the surgical scars left by laparoscopic surgeries is very small; it only needs a short hospital stay, and can promote the early recovery. Compared with the traditional open surgeries, LC improves the outcome and is regarded as the standard-of-care of the cholecystitis treatment.^[5,6]^ In the United States, there are about 750,000 LCs per year, and the trend is expected to increase.^[7]^

Preoperative anxiety is a familiar phenomenon in patients undergoing preoperative assessment. It refers to the process from the start date of a specific operation to the gradually intensified process at the beginning of the operation.^[8]^ In general, it can be described as a very disturbing situation for the patients. Anxiety leads to increased pain, increased consumption of analgesics, and prolonged hospital stay, and direct impact on the medical costs.^[9,10]^ Preoperative nursing visit is one of the most effective and safest ways to offer education and psychological support for patients.^[11]^ This visit offers a chance to collect the data to better manage patients in the surgery process and to educate patients on how to cooperate with their medical care and surgical team. An informed surgical patient undergoes less anxiety and fear. Blay and Donoghue ^[12]^ have reported that the preadmission intervention of education can help decrease the levels of pain after LC, and remarkably improve the knowledge of patients’ self-care and management of complication.

However, the efficacy of preoperative nursing visits remains unclear in LC patients. We perform this randomized clinical trial protocol to study the effects of nursing visits against the preoperative anxiety and postoperative complications in patients undergoing LC. We will offer the patients with education and information about the operating room, surgical procedures, anesthesia, and preoperative and postoperative care.

## Methods

2

### Study design

2.1

This is a single center, placebo-controlled randomized trial that will be performed from August 2020 to December 2020. The trial is performed in accordance with the SPIRIT Checklist for randomized studies. It is authorized by the Ethics Committee of Taizhou Hospital of Zhejiang Province (D20211-34) and then is registered in research registry (researchregistry5924). The surgeon will explain the details of trial, afterward, patiently answer all the questions from patients. These patients are then presented with the written information of our trial. Each patient receives a written informed consent. As all patients participated voluntarily, they could withdraw at any time during the trial.

### Inclusion of exclusion criteria

2.2

Candidates for inclusion are patients aged 18 to 60 years old with elective LC; ASA I-II classification; and normal platelet coagulation and count function. Exclusion criteria are as follows: patients with potential mental or physical illness; patients with the history of surgery or taking a specific drug; and severe kidney, liver, lung, and heart diseases.

### Subjects

2.3

Two hundred patients undergoing LC will be included in this study. In the random envelope, all participants will be assigned a random number via utilizing the random number table, and the result of allocation is hidden. Patients are randomly divided into 2 groups: experiential group (n = 100) or control group (n = 100). Physicians, statisticians, data collectors, and evaluators are all blinded to the allocation.

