### Intervention

2.4

The experimental group is given a preoperative nursing visit to each patient 1 day before the operation, whereas the control group not receive preoperative nursing intervention. Preoperative anxiety and the postoperative complications, involving nausea and vomiting, and pain are then investigated for 30 minutes between the experimental group and control group. Anxiety is assessed through utilizing the Spielberger State-Trait Anxiety Inventory,^[13]^ which was translated and then proved in Iranian population. Afterwards, 2 independent psychologists examine the questionnaire for any mistranslation or bias. The questionnaire composes of 20 items and is divided into two 10-question parts to determine trait anxiety or state. It is scored from 1 (no anxiety) to 4 (the highest anxiety level) on the basis of anxiety intensity, with a total score of 20 to 80. The pain is detected utilizing the visual analogue scale. And nausea and vomiting is measured through utilizing the Johnson 10 scale criteria. The data collection involves reviewing the medical records of patients and then performing the face-to-face interviews. Patients in experimental group are interviewed the day before the operation. The interviews contain asking patients about their concerns about surgery plans and procedures, and then answering their questions in easy-to-understand phrases. The patients in experience group also receive education on the surgery team and the environment of operating room, the process of anesthesia, advantages of laparoscopic surgery, and the postoperative care from recovery room to discharge. The primary outcomes include State-Trait Anxiety level and postoperative visual analogue scale. Secondary outcomes included total consumption of analgesics and postoperative complications.

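### The trial is labelled placebo-controlled although controls get no visit and no sham, both primary outcomes are patient-rated, and the described interview blurs the visit with blinded data collection

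*Protocol article*

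**What the plan says.** The Study design section states: "This is a single center, placebo-controlled randomized trial that will be performed from August 2020 to December 2020". The Methods part of the Abstract uses the same label. The Intervention section gives the experimental group a nursing visit on the day before surgery, "whereas the control group not receive preoperative nursing intervention". No sham or attention visit appears anywhere in the article.

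On blinding, the Subjects section says: "Physicians, statisticians, data collectors, and evaluators are all blinded to the allocation". Patients and the nurses who make the visits are not on that list. At consent, according to Study design, "The surgeon will explain the details of trial, afterward, patiently answer all the questions from patients".

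On outcomes, the Intervention section says: "The primary outcomes include State-Trait Anxiety level and postoperative visual analogue scale". For the first of these, "Anxiety is assessed through utilizing the Spielberger State-Trait Anxiety Inventory". Pain is scored on the VAS. On how data are obtained, the same section says: "The data collection involves reviewing the medical records of patients and then performing the face-to-face interviews". Shortly after comes: "Patients in experimental group are interviewed the day before the operation". The article then describes the interviews as asking about patients' concerns and answering their questions, and adds that experimental patients also receive education.

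**The concern.** A placebo label tells the reader that the comparison holds attention and expectation roughly equal between arms. This design does not do that. One arm is visited and the other is not, and the people who supply both primary scores can tell which arm they are in. Blinding an evaluator gives little protection to a score that the patient provides.

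The second difficulty is the word interview. The article uses it for data collection and, almost immediately, for a supportive conversation described only for the experimental arm. If these are the same contact, whoever conducts it knows the allocation, and the claim that data collectors are blinded fails for that person. Assessment conditions would then also differ between arms beyond the visit itself.

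At stake is how a positive result is read. A difference in anxiety or pain could reflect the visit, expectation, or the setting in which the scores were taken. The stated placebo control and blinding would lead a reader to discount the last two.

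**Working it through.** The main check compares statements; the article gives no figure on this point to reproduce.

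**Control label.** Study design and the Abstract assert placebo control. The Intervention section and the Abstract say that controls do not receive the nursing visit. With no sham described, these statements cannot both be true.

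**Who knows the allocation.**
- *Patients:* not listed as blinded; the trial is explained to them; they either receive a visit or do not. That they know their arm is an inference, but a strong one.
- *Visiting nurses:* they know the arm by definition and are not listed as blinded.
- *Statisticians, physicians, record reviewers:* blinding is feasible, and nothing in the text rules it out.
- *Data collectors:* listed as blinded, but the only interview described in detail belongs to the experimental arm and has the content of the visit. The article does not say who conducts it or who collects the anxiety and VAS scores.

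**Size of the possible effect (illustration only).** Inputs from the article: 100 patients per arm (Subjects) and a significance level of .05 (Statistical analysis). Assumptions: a two-sided test (the article does not state sidedness), a normal approximation, no true effect, and a reporting bias of *d* SD favouring the visit. The article gives no SD, effect size or power, so *d* is varied from 0.1 to 0.3.

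Standard error in SD units: √(2/100) = 0.1414.

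P(significant in favour of the visit) = Φ(d/0.1414 − 1.960)

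| d (SD) | d/0.1414 | minus 1.960 | Probability |
|---|---|---|---|
| 0 | 0 | −1.960 | 0.025 |
| 0.1 | 0.707 | −1.253 | 0.105 |
| 0.2 | 1.414 | −0.546 | 0.293 |
| 0.3 | 2.121 | 0.161 | 0.564 |

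These apply to each primary outcome separately. Counting significance in either direction, the 0.1 SD row becomes 0.109; the 0.2 and 0.3 SD rows still round to 0.293 and 0.564.

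For scale, the difference detectable with 80% power at this size is 0.1414 × (1.960 + 0.842) = 0.396, about 0.40 SD. Each assumed bias is smaller than that.

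**The case against.** The label has no good defence, but several points can fairly be made against the rest.

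- The blinding sentence does not claim that patients or visiting nurses are blinded. Patients knowing their arm is the ordinary limit of any visit versus no-visit trial and contradicts nothing on that list. This stands: the absence of patient blinding is not itself the error.
- The Intervention section also says that anxiety, nausea and vomiting, and pain are investigated afterwards in both groups. That suggests a separate assessment step, with the day-before interview being simply the visit. This stands in part. It is a plausible reading, but the text places the interview directly under data collection and does not separate the two.
- A reader might infer that blinded data collection is impossible here, or that patients give flattering answers to the nurse who visited them. The article supports neither. It never says that the visiting nurse administers the inventory or the VAS, separate blinded staff could collect the scores, and the VAS primary is postoperative.
- Contact before assessment differs between arms because that is the intervention, and the article's conclusion already credits the visit as a whole rather than the education alone. This stands.
- The bias sizes are assumed, and the calculation is the power curve at 100 per arm. This stands: it shows what a modest bias could do, not that one exists in this trial.

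**Conclusion.** The concern holds in a limited form. The placebo label is wrong on the article's own account of the control arm. The blinding of data collectors conflicts with the Intervention section on its most direct reading, but because the collector of the scores is not identified, the right description is unclear and in need of correction, not impossible. Both primary outcomes are affected, since both are rated by patients who will in practice know whether they were visited.

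The chance of a significant result in favour of the visit with no true effect rises from 2.5% to about 11%, 29% or 56% if reporting bias is 0.1, 0.2 or 0.3 SD. This rests on those assumed biases, a two-sided .05 test and 100 per arm. The percentages illustrate the risk and are not a gain the fix would deliver, because patients' knowledge of their arm would remain.

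**What to change.** 1. In the Abstract and Study design, replace the placebo label with: *no-visit (usual care) controlled; patients and visiting nurses not blinded*.
2. In Subjects, restrict the blinding statement to the roles that can be blinded, and say who collects the anxiety and VAS scores.
3. In Intervention, separate the visit interview from outcome collection. Have the anxiety form and VAS completed in both arms at the same time points and collected by existing staff who took no part in the visits.
4. Interpret any difference as visit versus no visit, including expectation effects, and state patients' knowledge of their arm as a limitation.

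The cost is wording plus a rule on who handles the existing forms. This assumes that the data collectors the article already lists as blinded are not the visiting nurses; the article gives no staffing detail. The downside is a weaker, but true, control and blinding claim. The change reduces interviewer bias only. The separation must be in place before outcomes are collected, since it cannot be restored afterwards.

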### Intervention

2.4

The experimental group is given a preoperative nursing visit to each patient 1 day before the operation, whereas the control group not receive preoperative nursing intervention. Preoperative anxiety and the postoperative complications, involving nausea and vomiting, and pain are then investigated for 30 minutes between the experimental group and control group. Anxiety is assessed through utilizing the Spielberger State-Trait Anxiety Inventory,^[13]^ which was translated and then proved in Iranian population. Afterwards, 2 independent psychologists examine the questionnaire for any mistranslation or bias. The questionnaire composes of 20 items and is divided into two 10-question parts to determine trait anxiety or state. It is scored from 1 (no anxiety) to 4 (the highest anxiety level) on the basis of anxiety intensity, with a total score of 20 to 80. The pain is detected utilizing the visual analogue scale. And nausea and vomiting is measured through utilizing the Johnson 10 scale criteria. The data collection involves reviewing the medical records of patients and then performing the face-to-face interviews. Patients in experimental group are interviewed the day before the operation. The interviews contain asking patients about their concerns about surgery plans and procedures, and then answering their questions in easy-to-understand phrases. The patients in experience group also receive education on the surgery team and the environment of operating room, the process of anesthesia, advantages of laparoscopic surgery, and the postoperative care from recovery room to discharge. The primary outcomes include State-Trait Anxiety level and postoperative visual analogue scale. Secondary outcomes included total consumption of analgesics and postoperative complications.

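### The only anxiety score the protocol defines adds 10 state and 10 trait items, and the anxiety primary outcome does not name the state part

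*Protocol article*

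**What the plan says.** Section 2.4 (Intervention) sets out the anxiety questionnaire: "The questionnaire composes of 20 items and is divided into two 10-question parts to determine trait anxiety or state". Each item is graded from 1 to 4, "with a total score of 20 to 80". No separate score or range is given for either part.

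The same section states: "The primary outcomes include State-Trait Anxiety level and postoperative visual analogue scale". The Abstract says the same. Neither place says whether the state part, the trait part or the total is to be compared, and section 2.5 (Statistical analysis), which lists t tests and an analysis of variance for repeated measurements, does not say so either.

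The intervention is a single contact: "The experimental group is given a preoperative nursing visit to each patient 1 day before the operation". The Introduction gives the aim as to "study the effects of nursing visits against the preoperative anxiety and postoperative complications in patients undergoing LC".

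**The concern.** The protocol separates two constructs and then gives a score only for their sum. Its question is about the first construct: how anxious the patient is as the operation approaches. Trait items ask how a person generally is, and one visit on the day before surgery has little reason to change that.

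If the total serves as the anxiety primary outcome, half of that outcome's items carry little expected effect but full between-patient variance. A real effect on state anxiety is then harder to detect. If the parts are to be scored separately, the outcome as named covers two scores with no choice between them. Either way the anxiety endpoint is not fixed on the quantity the trial sets out to change.

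**Working it through.** **Step 1. The stated range.**
- All 20 items: 20 × 1 = 20 and 20 × 4 = 80. This reproduces the protocol's range.
- One 10-item part: 10 × 1 = 10 and 10 × 4 = 40.

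So the only score defined is the sum of the state and trait parts.

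**Step 2. Inputs for the size of the effect.**
- From the protocol: 100 patients per arm (section 2.3), independent-samples t test and significance at 0.05 (section 2.5).
- Assumed, because the protocol gives no effect size, SD, correlation or power: a two-sided test; a single comparison of post-visit scores; a state effect of d state SDs; equal SDs for the two parts; correlation r between them; no effect on the trait part.

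**Step 3. Formula.** In units of the state SD, the variance of the sum is 1 + 1 + 2r = 2(1 + r). The raw mean difference in the sum is still d, because the trait part adds nothing to it. Hence

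d_total = d / √(2(1 + r)).

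**Step 4. Results at d = 0.4, 100 per arm (two-sample t power).** On the state part alone, power is 80%. On the total:

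| r | d_total / d | d_total | Power |
|---|---|---|---|
| 0 | 0.71 | 0.283 | 51% |
| 0.3 | 0.62 | 0.248 | 42% |
| 0.5 | 0.58 | 0.231 | 37% |
| 0.7 | 0.54 | 0.217 | 33% |

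By the normal approximation, 80% power needs 99 per arm on the state part and 197 (r = 0) to 334 (r = 0.7) per arm on the total.

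**Step 5. Sensitivity to the assumptions.**
- *Effect size*, r from 0 to 0.7. At d = 0.3, power falls from 56% to between 32% and 21%. At d = 0.5, it falls from 94% to between 70% and 48%. At d = 0.7, the total still has 86% (r = 0.3) to 76% (r = 0.7).
- *Unequal SDs.* With k the ratio of trait SD to state SD, the factor is 1 / √(1 + k² + 2rk). For k from 0.75 to 1.25 and r from 0 to 0.7 it lies between 0.80 and 0.48.
- *Trait answers move half as much as state answers.* The factor is 1.5 / √(2(1 + r)), which is 0.93, 0.87 and 0.81 for r = 0.3, 0.5 and 0.7. At r = 0 it is 1.06, so the loss disappears only near zero correlation, which is unlikely for two parts of one anxiety inventory.
- *Change from baseline analysed.* Assume a retest correlation of 0.5 for state, giving a change variance of 2(1 − 0.5) = 1, and of 0.9 to 1.0 for trait, giving 2(1 − 0.9) = 0.2 down to 0. With a correlation between the two changes of 0 to 0.3, the largest variance of the summed change is 1 + 0.2 + 2 × 0.3 × √0.2 = 1.47, a factor of 1/√1.47 = 0.83. The smallest is 1, a factor of 1.00. Power at d = 0.4 is then 64% to 80%.

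**Step 6. Trait as a covariate instead.** With the state score as outcome and a pre-visit trait score as covariate, the effect becomes d / √(1 − r²). At d = 0.4 this gives 0.419, 0.462 and 0.560 for r = 0.3, 0.5 and 0.7, with power of 84%, 90% and 98%.

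**The case against.** The strongest reply is that use of the total is inferred. Section 2.4 presents the two parts as measuring different things, the 20 to 80 range may simply describe the instrument, and no sentence says the total will be compared between arms. The outcome's name echoes the questionnaire's name and would fit separate reporting of both parts. The full protocol, the analysis plan and Figure 1 are not at hand. This stands to the extent that the point must be conditional on the total being used. It does not remove the point: the article does define a score, that score is the sum, and the state part is nowhere made the endpoint.

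The second reply is that the loss in power depends on a post-only comparison. Section 2.5 mentions paired tests and repeated measurements. It does not say that anxiety is among them, but if it is, a stable trait largely cancels from the change score and most of the loss goes with it. This also stands, as Step 5 shows.

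Two stronger readings are tempting and should be resisted. A reader might infer that half the primary outcome is trait. The postoperative visual analogue scale is a second primary outcome, so at most this is half the items of one of two. A reader might also infer that a difference in the total says nothing about state anxiety. If trait does not move, the expected raw difference in the total equals the state difference exactly. What is lost is precision, and the total alone cannot show which part moved.

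**Conclusion.** The point holds in conditional form. It is certain from the protocol's own arithmetic that the one defined score sums state and trait items, and that the primary outcome names no part. It is likely, but not stated, that the total would be compared.

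If it is, and only post-visit scores are used, the standardised effect is about 54% to 71% of the state effect under equal SDs and no trait change, with the power loss shown in Step 4. The inputs behind those figures are assumptions, as is the stability of trait anxiety, which rests on what the word means and not on anything the protocol says. The documents therefore support a poorly chosen or unfixed score, not a demonstrated loss of a given size. Severity: should fix.

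**What to change.** In section 2.4, name the 10-item state score (range 10 to 40), completed after the visit and before surgery, as the anxiety primary outcome, and state that the 20 to 80 total is not primary.

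Where the trait part can be completed before the visit in both arms, for example at consent, use it as a baseline covariate. Otherwise report it descriptively.

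The text change is a few sentences, with the same form and the same patients. There are two costs. A 10-item score is somewhat less reliable than a 20-item one. Early trait collection also requires giving the form to controls at the same time point as the experimental group; section 2.4 describes a day-before interview for the experimental group only, so this may mean an added contact. The covariate gain in Step 6 depends on that step. The choice of score should be made before any outcome data are seen.

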### Statistical analysis

2.5

For data analysis, the SPSS 20.0 is employed. The patients’ descriptive characteristics are compared using the Chi-square test in the study and control groups. Paired-samples *t* test and independent samples *t* test are utilized to compare the patients’ values between the 2 groups. Variance analysis was utilized to compare the repeated measurements. A *P* < .05 is regarded the significant in statistics.

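### Two unranked primary outcomes share one unadjusted P < .05 with no success rule; if either one suffices, the type I error on the primary claim is up to about 10%

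*Protocol article*

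**What the plan says.** The Abstract (Methods) and section 2.4 name the same pair of primary outcomes. Section 2.4 reads: "The primary outcomes include State-Trait Anxiety level and postoperative visual analogue scale". Neither place ranks anxiety above pain or pain above anxiety.

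On the anxiety instrument, section 2.4 says: "The questionnaire composes of 20 items and is divided into two 10-question parts to determine trait anxiety or state". It also gives one total running from 20 to 80. It does not say which score is the primary one, and it does not fix one analysis time for each primary outcome.

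Section 2.5 gives the only decision threshold in the document: "A *P* < .05 is regarded the significant in statistics". On methods it says: "Paired-samples *t* test and independent samples *t* test are utilized to compare" values between the groups, and it adds an analysis of variance for repeated measurements. No method is tied to a particular primary outcome. The document contains no alpha split, no testing order and no adjustment, and does not say whether one or both primary results must be significant.

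On size, section 2.3 says: "Two hundred patients undergoing LC will be included in this study", with 100 allocated to each group.

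**The concern.** With two primary outcomes, a threshold of .05 per test does not by itself fix the error rate of the trial's main claim. That rate depends on the success rule. If the claim may rest on anxiety alone or on pain alone, there are two chances of a false positive at 5% each. If it needs both, there is no inflation and the price is power.

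The document leaves both readings open. A significant result on one outcome and not the other could be reported as a positive trial, and the reading could be chosen after the results are seen. Both the Abstract and the Conclusion section already anticipate that the visit may reduce anxiety and complications, so it matters which pattern of results would count as support.

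**Working it through.** **Inputs**
- Number of primary outcomes: 2 (Abstract, Methods; section 2.4).
- Threshold per test: .05 (section 2.5). Two-sided testing is assumed, as sidedness is not stated.
- Patients per arm: 100 (section 2.3).
- Correlation between the anxiety and pain test statistics: not given, so a range is shown.

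The plan has no figure to reproduce. It states no familywise error rate, and it gives no effect size, standard deviation or power for the 200 patients.

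**Error if either outcome suffices, with no effect on either**

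Independent tests: 1 − (1 − 0.05)² = 1 − 0.9025 = 0.0975.

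Upper bound for any correlation (Bonferroni inequality): 0.05 + 0.05 = 0.10.

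Simulated two-sided normal tests with 4 million draws per row:

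| Assumed correlation | At least one P < .05 |
|---|---|
| 0.3 | 9.5% |
| 0.5 | 9.1% |
| 0.7 | 8.4% |
| 0.9 | 7.0% |

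Against the nominal 5%, the independent case is 9.75 / 5 = 1.95 times, an excess of 4.75 percentage points. These figures count false positives in either direction. Counting only those that favour the visit, the independent case is 1 − (1 − 0.025)² = 4.94% against 2.5% for one test, so the near-doubling is the same.

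**Error if both must be significant**

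A false claim requires a P < .05 on at least one outcome that has no effect, and it needs that outcome to be significant along with the other. Its probability therefore cannot exceed 0.05. With no effect on either outcome and independent tests it is 0.05² = 0.0025.

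**Error under Holm**

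The smaller P value is compared with .025 and, only if it passes, the larger with .05. With no effect on either outcome and independent tests, the chance of any rejection is 1 − (1 − 0.025)² = 4.94%. Holm keeps the familywise error at or below 5% whatever the correlation.

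**Cost in detectable difference (80% power, 100 per arm, normal approximation)**

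d = (z for 1 − α/2 + z for 0.80) × √(2/100)
- α = .05: (1.960 + 0.842) × 0.1414 = 0.396, about 0.40 SD.
- α = .025: (2.241 + 0.842) × 0.1414 = 0.436, about 0.44 SD.

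Holm's cost lies between these two values, because the second test returns to .05 once the first has passed.

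**Cost of requiring both**

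At a true difference of 0.40 SD, one test at .05 has power 0.807. If both outcomes have that difference and the tests are independent, the power for both is 0.807² = 0.65. Positive correlation raises it, but never above 0.807.

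**The case against.** The strongest reply is that success rules and alpha allocation often sit in a statistical analysis plan, that none is shown here, and that a journal article condenses the full protocol. Section 2.5 gives a convention for calling a P value significant. It does not claim a 5% trial-wide rate and does not exclude an adjustment elsewhere. This limits how much can be asserted, but it does not remove the point. The article itself chose two unranked primary outcomes and one unadjusted threshold, and followed as written these permit the inflated error. Nothing in it refers to a further rule.

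Three stronger readings are tempting and are not supported:

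- **Any single P < .05 counts as success.** A reader might infer this, but the document does not state it. It is one of two permitted readings, and under the other the error stays at or below 5%.
- **Three primary tests, with an error of about 14%.** Treating state, trait and pain separately gives 1 − 0.95³ = 14.3% if independent. Section 2.4, however, names one anxiety level and gives one 20 to 80 total, and nowhere says that the two parts are separate primary tests. The count that the text supports is two. Which score is primary still needs naming.
- **Repeated measurements as extra chances.** Section 2.5 assigns these to an analysis of variance, which can be one joint analysis. No set of separate tests by time point is described for the primary outcomes.

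**Conclusion.** The point holds in a conditional form. The document fixes two unranked primary outcomes under one unadjusted .05 and leaves the success rule open. If either outcome suffices, the familywise error is 9.75% under independence, about 9% at an assumed correlation of 0.5, and at most 10%. If both are required, it is at most 5%.

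The figures assume two-sided tests, one test per primary outcome and, for the either-one case, no effect on either outcome. The correlations are assumptions. The conclusion does not depend on how the sample size was reached.

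It also does not follow that the trial must drop to one primary outcome. Making state anxiety the sole primary outcome, with pain tested after it or demoted, would control the error, but it changes the stated objectives. The documents do not rank anxiety above pain or the state part above the total.

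**What to change.** Add two or three sentences to section 2.5, with matching wording in section 2.4 and the Abstract, before any outcome is compared by group:

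1. State the success rule. Either test the two primary outcomes with Holm's procedure at an overall two-sided .05, or declare that both must be significant at two-sided .05.
2. Name one anxiety score and one time point for anxiety, and one time point for the pain scale. Identify the between-group test that decides each.
3. Say that analgesic consumption and postoperative complications are supportive, reported with estimates and confidence intervals, and cannot carry the primary claim.

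No extra patients or measurements are needed. Under Holm, the detectable difference rises by at most about 0.04 SD (0.44 − 0.40). Requiring both keeps each test at .05 but lowers the chance of overall success, to about 65% in the independent 0.40 SD example. The sponsor should choose according to whether an effect on one outcome alone would be enough to support the visit.
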